## Materials and methods

### Study design

This prospective randomized controlled intervention received approval from the Institutional Review Board of Incheon St. Mary’s Hospital (OC24FISI0032) on April 22, 2024. The protocol complies with the Helsinki Declaration and Good Clinical Practice guidelines. Participants will be divided into three groups: intervention group 1 (PA and PST), intervention group 2 (PA), and a control group (no intervention).

Initially, the two intervention groups will be categorized by age. We will randomly assign 18 children and their parents to each group, resulting in 72 participants, using a random number generator (version 1.1). The control group will consist of 18 children and their parents (36 participants) selected from those unable to participate in the interventions but who could complete the assessments. Therefore, the total number of participants across all groups will be 54 children, 54 parents, and 108 individuals.

To enhance the robustness of the analysis and mitigate potential biases from participant dropout, an intention-to-treat (ITT) approach will be implemented. All randomized participants will be analyzed regardless of intervention adherence. Missing data will be managed using multiple imputation methods to preserve data integrity and minimize bias. Additionally, sensitivity analyses will be conducted to evaluate the potential impact of missing data on the study outcomes.

All participants in this study will continue to receive their existing medication treatments throughout the intervention period. Before proceeding with the assessments and interventions, the children and their parents will provide written informed consent. Recruitment and data collection began on May 31, 2024 and is expected to end on February 28, 2025. Data collection and results are expected to be completed by September 30, 2025. Details of the research procedure are presented in Fig 1.

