### Statistical analysis

The normality of the primary variables will be assessed using the Shapiro-Wilk test, and homogeneity of variances will be evaluated using Levene’s test. If normality is satisfied, a repeated measures ANOVA will be performed to examine the main effects of time, group, and their interaction. Mauchly’s test for sphericity will be conducted, and if violated, the Greenhouse-Geisser correction will be applied. If the normality assumption is violated, non-parametric alternatives will be implemented. The Kruskal-Wallis test will be used for between-group comparisons at each time point, while the Friedman test will be applied for within-group repeated measures. To adjust for multiple comparisons, Bonferroni correction will be applied as needed to control for Type I error. If significant interaction effects are observed in the repeated measures analysis, post-hoc tests will be conducted. For parametric statistics, paired t-tests will be used to compare within-group differences over time, and independent t-tests will be performed to compare mean differences between groups at the same time points. For non-parametric statistics, the Mann-Whitney U test will be used to compare two groups at a specific time point, and the Wilcoxon signed-rank test will be employed to analyze within-group differences between two time points.

All data collected in this study will be analyzed using SPSS 26 statistical software. The five subscales and total score of the Wechsler assessment will be analyzed separately. Since multiple comparisons will be made, a multiple comparisons issue may arise. To address this, the Bonferroni correction will be applied, setting the significance level to 0.0167. For other variables, the significance level will be set to 0.05 for analysis.

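### Letting a normality pre-test choose between repeated measures ANOVA and rank tests fits badly with multiple imputation: the branch can differ between imputed data sets, and the rank branch has no group-by-time result to pool

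*Protocol article*

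**What the plan says.** Under Study design, the protocol article adopts intention-to-treat: "All randomized participants will be analyzed regardless of intervention adherence". On incomplete data it states: "Missing data will be managed using multiple imputation methods to preserve data integrity and minimize bias". It also promises sensitivity analyses for missing data.

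Under Statistical analysis, the test depends on the data. First, "The normality of the primary variables will be assessed using the Shapiro-Wilk test". Then, "If normality is satisfied, a repeated measures ANOVA will be performed to examine the main effects of time, group, and their interaction". Otherwise, "If the normality assumption is violated, non-parametric alternatives will be implemented": Kruskal-Wallis between groups at each time point and Friedman within groups over time. Post-hoc tests follow a significant interaction. They are paired and independent t-tests on the parametric side, and Mann-Whitney and Wilcoxon signed-rank tests on the other.

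On sphericity the section says: "Mauchly’s test for sphericity will be conducted, and if violated, the Greenhouse-Geisser correction will be applied". It does not mention imputation.

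**The concern.** Multiple imputation presumes one analysis, run identically on every completed data set and then combined. The Statistical analysis section instead lets a normality result select the analysis, and the two possible analyses answer different questions. The ANOVA branch tests whether change over time differs between groups. The rank branch compares groups one visit at a time and visits one group at a time, so it never tests that difference in change.

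Two things are at stake. First, if the imputed data sets disagree on normality, some call for an interaction F-test and others for a set of rank tests, with nothing common to combine. Second, if the rank branch is taken, the trial's central group-by-time question gets no test and no pooled effect estimate. The trigger for post-hoc comparisons, a significant interaction, also has nothing to act on.

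This is a mismatch between two rules that the article states. It does not depend on the absence of an imputation model, a number of imputations or a pooling formula, which may properly sit in a full protocol or analysis plan.

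**Working it through.** **1. What can be pooled.** Rubin's rules need an estimate and its variance from each of M imputed data sets. The pooled estimate is the mean, and its variance is W + (1 + 1/M)B, with W the average within-imputation variance and B the between-imputation variance.

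| Planned analysis | Estimate with variance? | Group-by-time test? |
|---|---|---|
| Repeated measures ANOVA interaction | Yes: (3 − 1)(3 − 1) = 4 mean contrasts with a covariance matrix | Yes |
| Paired and independent t-tests | Yes: mean differences with standard errors | As follow-up |
| Kruskal-Wallis at each visit | No | No |
| Friedman within each group | No | No |
| Mann-Whitney, Wilcoxon signed-rank | Not from the tests as named | No |

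A simulation confirms that the parametric branch is workable. It used 3 groups of 18, 3 visits, normal data, correlation 0.5, 20% monotone dropout, 20 imputations and 1,000 trials with no effect. The four interaction contrasts could be pooled in every trial, and the pooled test rejected in 5.1% at a nominal 5%. Kruskal-Wallis p-values could be combined on a normal scale (about 5.5% rejection, with a few non-finite transforms counted as non-rejections). That yields a p-value but no effect estimate and still no interaction test.

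**2. How often the branch differs between imputations.** Group size, number of visits and dropout come from the Sample size section. Normality, correlation 0.5, the dropout pattern and M = 20 are assumptions. A verdict of non-normal means that any tested cell has Shapiro-Wilk p < 0.05.

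- Three groups at the last visit: the verdict was not the same in all 20 imputed data sets in about 55% of trials. A repeat with 600 trials also gave 55%.
- All nine arm-by-visit cells: 59% of 600 trials, and about 60% in a further run. In 46% of the 600 trials each verdict held in at least 10% of the imputations, so the split was often not down to one stray data set.
- With assumed correlations of 0.3 and 0.7 in place of 0.5, the verdict still differed in more than half of trials.

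A different figure should not be confused with these. The chance that at least one of nine independent tests rejects in a single normal data set is 1 − 0.95^9 = 0.37. It shows how easily the rank branch is entered by chance. It does not measure disagreement between imputations of one data set, which share all observed values.

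**3. The power figures that might be attached to this point.** The interaction test has noncentrality λ = N·m·f²/(1 − ρ), df1 = 4 and df2 = 2(N − 3), with m = 3, f = 0.25 and α = 0.0167 from the Sample size section. The article states no correlation ρ.

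- Plan's figure, N = 45, ρ assumed 0.5: λ = 45 × 3 × 0.0625/0.5 = 16.875, df2 = 84, power 0.814. The stated 45 is reproduced under that assumption.
- Complete cases after 20% loss: 54 × 0.8 = 43.2, so 43, with df2 = 80 and 43 × 3 × 0.0625 = 8.0625.

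| Assumed ρ | λ at N = 43 | Power |
|---|---|---|
| 0.3 | 8.0625/0.7 = 11.52 | 0.60 |
| 0.5 | 8.0625/0.5 = 16.125 | 0.79 |
| 0.7 | 8.0625/0.3 = 26.875 | 0.97 |

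These values belong to a complete-case analysis that the plan does not propose.

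**The case against.** The strongest defence is that multiple imputation followed by ANOVA contrasts and t-tests is a workable analysis, and the calculations above bear this out. Nothing in the article says that normality will be re-tested in each imputed data set. A single check on the observed data would fix one branch for all imputations. Where that check is made, and how results are combined, are details that a condensed article may leave to a fuller document.

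Much of this stands. It removes several stronger readings that a reader might infer:

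- That the intention-to-treat analysis cannot be carried out at all. The parametric branch pools in the ordinary way, and even rank-test p-values can be combined ad hoc.
- That the sphericity test also selects the branch. Mauchly's test only switches a degrees-of-freedom correction within the ANOVA.
- That the analysis would fall back to complete cases. Study design says the opposite.
- That power of 0.79 follows from the plan's own inputs. It needs an assumed correlation of 0.5, and the range is 0.60 to 0.97.

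What the defence does not answer is the rank branch itself. One check on observed data stops the branch flipping, but if that check fails, the stated analysis has no group-by-time test and no estimate for Rubin's rules. The article fixes that outcome in its own text, so it is not a detail left for later.

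**Conclusion.** The point holds in a limited form. A normality pre-test that switches between a group-by-time ANOVA and separate rank tests is poorly matched to the multiple imputation that the article promises. If the pre-test is run in each imputed data set, the branch differs between imputations in about 55 to 60% of simulated trials even when the data are normal. That figure rests on the assumed correlation, dropout pattern and number of imputations, and on letting any one rejecting cell decide. If the pre-test is run once, the disagreement goes away, but the rank branch still leaves the main question without a test or a poolable estimate.

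No loss of power and no exclusion of families is shown to follow from the plan as written. The case for change is that the remedy is cheap and keeps the group-by-time question answerable whatever the pre-test shows.

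The intention-to-treat wording refers to randomised participants, while the 18 control children are "selected from those unable to participate in the interventions but who could complete the assessments". The change proposed here does not address that separate matter.

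**What to change.** Remove the normality pre-test as a switch between methods. Pre-specify one main analysis for each outcome: a likelihood-based mixed model for repeated measures on all observed visits, reporting group-by-time contrasts with standard errors and confidence intervals. For the K-WISC-V, which is given at only two assessments, the same model has a single follow-up contrast per group comparison.

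Keep multiple imputation, applied to those same contrasts, as the missing-data sensitivity analysis that Study design already promises. A shift applied to the imputed values would let it examine departures from missing at random. Use rank-based or bootstrap versions only as sensitivity analyses, reported alongside the main result whatever a normality check shows.

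The cost is revised analysis wording and a different procedure in the analysis software, with no added data. The main downside is that the primary result then relies on missing at random, which the sensitivity analysis is there to probe.

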**Fig 1 pone.0325669.g001:**
[figure not shown]
Schedule of enrolment, interventions, and assessments. IG: Intervention Group; CC: Control Group; PA: Physical Activity; PTS: Psychological Skills Training.

### Participants

#### Selection criteria and recruitment.

Participants for this study will be recruited using purposive sampling, a type of non-probability sampling. Eligible participants will be children diagnosed with ADHD by pediatric psychiatrists at local child and adolescent psychiatry clinics and regional tertiary hospitals where the intervention is conducted. Recruitment announcements will be displayed on hospital screen bulletin boards and within the local community. The inclusion criteria for this study are as follows: 1) Children aged 6–12 years who have received a formal diagnosis of ADHD and are currently undergoing treatment; 2) Children for whom previous Wechsler test results confirm the absence of cognitive decline; 3) Children and parents where the primary caregiver is available to participate in the assessment and intervention. The exclusion criteria for this study include: 1) Children with significant cognitive decline; 2) Children with mental, physical, or medical conditions that would impede participation in PA or PST; 3) Children with any co-occurring disabilities other than ADHD; 4) Children whose primary caregiver is unable to participate; 5) Children involved in other research studies or exercise programs; 6) Children who struggle to cooperate with assessments and interventions. Among children diagnosed with ADHD receiving treatment, those who meet the inclusion/exclusion criteria and desire to participate will be selected.

### Sample size

The sample size for this study was determined through statistical analysis using the G*Power 3.1 program. Based on the data analysis method, the test family was set to F-tests, and the statistical test was designated as ANOVA: repeated measures, within-between interaction. The effect size was determined according to Cohen’s method [26] and was set to 0.25, based on previous studies [27–29]. Initially, the significance level (α) was set at 0.05 for the sample size calculation. However, to account for multiple comparisons, the Bonferroni correction was applied, adjusting the per-comparison significance level to α = 0.0167. The statistical power (1-β) was set at 0.80, the number of groups at three, and the number of repeated measurements at three. Consequently, the required sample size was recalculated to be 45 participants (15 per group). To account for potential attrition, a 20% dropout rate was considered, based on rates observed in previous studies [30–32]. Therefore, the final total sample size was 54 participants, with 18 participants allocated to each group.

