### Outcome measures

The final analysis will include data collected from a total of 54 children and their primary caregivers, with 18 children and their respective primary caregivers assigned to each of the two intervention groups and the control group: Intervention Group 1 (n = 36: 18 children, 18 parents), Intervention Group 2 (n = 36: 18 children, 18 parents), and the Control Group (n = 36: 18 children, 18 parents). Data from children and their primary caregivers will be analyzed separately.

The examiner will conduct the assessments while being blinded to the group assignment. Cognitive assessments will be administered by a certified clinical psychologist to quantitatively evaluate participants’ cognitive functions. Additionally, the physical activity level will be collected using the ActiGraph, and this data will be used to monitor the provided level of physical activity. The following assessment tools will be used for children with ADHD and their parents. For cognitive assessment, the Korean-Wechsler Intelligence Scale for Children, Fifth Edition (K-WISC-V) and the Visual-Motor Integration, Sixth Edition (VMI-6) will be used. For emotional assessment, the Revised Children’s Manifest Anxiety Scale (RCMAS) and the Children’s Depression Inventory (CDI) will be utilized. For behavioral assessment, physical activity levels will be measured using the Global Physical Activity Questionnaire (GPAQ). ADHD symptoms, social skills, and sleep quality will be evaluated using the Swanson, Nolan, and Pelham Questionnaire (SNAP), the Social Skills Rating System-Parent (SSRS-P), and the Korean Version of the Pittsburgh Sleep Quality Index (PSQI-K).

For primary caregivers, the assessment tools will include the GPAQ, the Parenting Stress Index-Short Form (PSI-SF), the Beck Anxiety Inventory (BAI), the Beck Depression Inventory (BDI), and the Korean Version of the Pittsburgh Sleep Quality Index (K-PSQI).

All groups will undergo three assessments for all measures except for the K-WISC-V. Intervention Groups 1 and 2 will be assessed before the intervention, immediately after the intervention (three months after the first assessment), and three months post-intervention. The control group will be assessed at baseline, after three months, and after six months. The K-WISC-V will be administered to all groups before the intervention and six months post-intervention. Detailed information about the outcome measures can be found in Table 3.

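### The 80% power is worked out for three groups, three measurements and alpha 0.0167, a combination that no planned interaction test uses; on the same inputs the K-WISC-V has about 69% with 45 analysed and the other outcomes about 91%.

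*Protocol article*

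**What the plan says.** The Sample size section of the protocol article reports a G*Power calculation in which "the statistical test was designated as ANOVA: repeated measures, within-between interaction". The effect size f "was set to 0.25, based on previous studies". A Bonferroni correction is then applied, "adjusting the per-comparison significance level to α = 0.0167". "The statistical power (1-β) was set at 0.80", with "the number of groups at three, and the number of repeated measurements at three". The result is 45 children, 15 per group, raised to 54 (18 per group) for 20% dropout. The section names no outcome for the calculation and gives no correlation between repeated measurements.

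Two other sections set the number of measurements and the alpha:

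- Outcome measures: "All groups will undergo three assessments for all measures except for the K-WISC-V". The K-WISC-V is given twice, once before the intervention and once at follow-up.
- Statistical analysis: the Wechsler subscales and total score are tested at 0.0167. "For other variables, the significance level will be set to 0.05 for analysis". The same section also allows a Bonferroni correction as needed, without attaching 0.0167 to anything other than the Wechsler.

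**The concern.** A power statement is useful only if its inputs match a test that will be run. Here the alpha is the Wechsler's, while the number of measurements is that of all the other outcomes. Side by side:

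| | Groups | Measurements | Alpha |
|---|---|---|---|
| Sample size section | 3 | 3 | 0.0167 |
| Planned: K-WISC-V | 3 | 2 | 0.0167 |
| Planned: all other outcomes | 3 | 3 | 0.05 |

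The first row matches neither of the others. A reader is likely to attach the 80% to every outcome, including the Wechsler, which the end of the Discussion cites among the reasons why the study matters. If the Wechsler has less power than that, a null cognitive result would be given more weight than it deserves. For the remaining outcomes the error runs the other way, and the stated figure undersells the design.

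**Working it through.** **Inputs from the protocol.** f = 0.25 (f² = 0.0625); k = 3 groups; alpha 0.0167 or 0.05; m = 2 or 3 measurements; N = 45 for analysis, 54 enrolled.

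**Assumed, because the article does not state them.** Correlation rho = 0.5 and sphericity (epsilon = 1). Sphericity matters only for the three-measurement tests; with two measurements it holds trivially.

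**Formula** (noncentral F, within-between interaction):

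- λ = f² × N × m / (1 − rho)
- df1 = (k − 1)(m − 1)
- df2 = (N − k)(m − 1)
- power = P(F′(df1, df2, λ) > critical F at alpha)

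**Step 1: reproduce the stated figure** (3 groups, 3 measurements, 0.0167). With N = 45, λ = 0.0625 × 45 × 3 / 0.5 = 16.875, df = 4 and 84, and power is 81.5%. With N = 42, λ = 15.75 and power is 77.6%. So 45 is the smallest N with equal groups that reaches 80%, as stated. Other correlations do not return 45: rho = 0.4 gives 54 and rho = 0.6 gives 36. Given sphericity, 0.5 is therefore the natural reading of the calculation.

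**Step 2: K-WISC-V as planned** (3 groups, 2 measurements, 0.0167).

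| N analysed | λ | df | Power |
|---|---|---|---|
| 43 (54 × 0.8 = 43.2) | 10.75 | 2, 40 | 66% |
| 45 | 0.0625 × 45 × 2 / 0.5 = 11.25 | 2, 42 | 69.2% |
| 54 | 13.5 | 2, 51 | 79.6% |

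With equal groups, 57 analysed children would be needed to pass 80%.

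**Step 3: all other outcomes as planned** (3 groups, 3 measurements, 0.05). With N = 45, λ is again 16.875 with df = 4 and 84, and power is 91.1%. N = 36 would be enough for 80%.

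**Step 4: sensitivity to the unstated correlation, N = 45.**

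| rho | K-WISC-V, 0.0167 | Other outcomes, 0.05 |
|---|---|---|
| 0.3 | 51% | 78% |
| 0.4 | 59% | 85% |
| 0.5 | 69% | 91% |
| 0.6 | 81% | 96% |
| 0.7 | 92% | 99% |

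**Step 5: sensitivity to carrying f = 0.25 over to two time points.** Suppose that the group difference follows a fixed profile over visits, and that the second K-WISC-V falls at the last point of that profile. Then f² is proportional to the variance of the profile across visits. At N = 45, rho = 0.5 and alpha 0.0167:

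- Effect present after baseline and fully sustained: the variance of (0, 1, 1) is 2/9 and of (0, 1) is 1/4. The ratio is 9/8, λ = 11.25 × 9/8 = 12.66, and power is 75%.
- Effect growing linearly to the last visit: the variance of (0, 0.5, 1) is 1/6 against 1/4. The ratio is 1.5, λ = 16.875, and power is 88%.
- Effect that halves after the end of the intervention: the variance of (0, 1, 0.5) is 1/6 and of (0, 0.5) is 1/16. The ratio is 0.375, λ = 4.22, and power is 25%.

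**The case against.** The best defence is that the Sample size section never claims 80% for the Wechsler. It names no outcome, its arithmetic is right, and for the large majority of outcomes (everything in Table 3 except the Wechsler) sizing at 0.0167 and testing at 0.05 is conservative. All of that stands, and it is why this is an inconsistency between sections and not a calculation error.

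The second defence is that 69% is not a fact about the plan. The correlation of 0.5 is inferred from a three-measurement calculation and then applied to a different instrument measured twice. At 0.6 the K-WISC-V already passes 80%, and a sustained or growing effect would also raise its power. This stands as a limit on the figure. It does not rescue the 80%, because a higher correlation or a different f for the Wechsler would be a new assumption that the article does not make, and a fading effect moves the figure sharply down.

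Third, the Outcome measures section speaks of 54 children in the final analysis, and 54 gives about 80% for the K-WISC-V. That needs complete data from everyone, whereas the sample-size reasoning itself allows for 20% loss. Multiple imputation keeps all children in the analysis but does not restore the information lost.

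Two stronger readings are tempting. A reader might take 0.0167 to be meant for the three pairwise group comparisons and power a two-group, three-visit interaction. The protocol plans no such test: its between-group post-hoc tests are t-tests or Mann-Whitney tests at single time points, and their power does not follow from an interaction f of 0.25. A reader might also replace 0.0167 by 0.05 divided by the six Wechsler scores. Whether the divisor of three is right is a separate question, and the mismatch described here does not depend on it.

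**Conclusion.** The inconsistency is established from the article alone: the combination that was powered (three measurements at 0.0167) is not used by any planned interaction test. Its size is conditional. With f = 0.25, sphericity and rho = 0.5, the K-WISC-V interaction has about 69% power with 45 analysed, against the stated 80%, and the three-measurement outcomes have about 91%. The K-WISC-V figure depends heavily on the correlation and on how the effect evolves over time, so a shortfall is the like-for-like result under the protocol's own inputs and not a certainty.

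A reader might infer that the trial as a whole is underpowered or that 45 is miscalculated. The documents support neither: 45 is correct for the design that was entered, and on the same inputs most outcomes have more power than stated.

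**What to change.** Rewrite the sample-size paragraph so that each power figure belongs to an analysis that will be run:

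1. State the assumed correlation between repeated measurements (0.5 reproduces 45) and the sphericity assumption.
2. For the outcomes measured three times, give the power at 0.05: about 91% with 45 analysed.
3. Give the K-WISC-V its own figure with two measurements and the alpha at which it will be tested: about 69% with 45 analysed at 0.0167, rho = 0.5 and f = 0.25. Alternatively, recompute it with a stated and justified retest correlation and effect size.
4. Do not leave the 80% figure standing for the Wechsler.

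The cost is one reworded paragraph and a less favourable stated power for the Wechsler. Enrolment, assessments and analyses stay as they are.

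### The 54 families planned cover 16.7% attrition, not the stated 20%: at 20% about 43 children complete, short of the required 45

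*Protocol article*

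**What the plan says.** All the figures are in the Sample size section of the protocol article.

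- **Model:** "the statistical test was designated as ANOVA: repeated measures, within-between interaction", run in G*Power.
- **Effect size:** Cohen's f "was set to 0.25, based on previous studies".
- **Significance level:** a Bonferroni step, "adjusting the per-comparison significance level to α = 0.0167".
- **Power and layout:** "The statistical power (1-β) was set at 0.80, the number of groups at three, and the number of repeated measurements at three".
- **Attrition:** "To account for potential attrition, a 20% dropout rate was considered", with earlier studies cited for the rate.
- **Result:** 45 required, 15 in each group, before attrition; after it, "the final total sample size was 54 participants, with 18 participants allocated to each group".

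The section does not print the formula that takes 45 to 54. It also gives neither the correlation between repeated measurements nor a nonsphericity value.

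Two other sections bear on the point. Study design commits to an intention-to-treat analysis and says "Missing data will be managed using multiple imputation methods to preserve data integrity and minimize bias". Outcome measures describes a final analysis of all 54 children and their caregivers.

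**The concern.** An attrition allowance has one purpose: after the expected loss, the number still under observation should be at least the number the power calculation asked for. A dropout rate is a share of those enrolled, so the required number is divided by one minus the rate. The printed 54 is what results from adding 20% of the required number instead. That gives a smaller total, and the requirement is then missed at the very attrition the authors expect.

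What is at stake is whether the stated sample size can be relied on. A reader of this section would conclude that one family in five can be lost with the target intact. That is not so.

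**Working it through.** **Inputs from the Sample size section:** required number 45 (15 per group); dropout 20%; enrolled 54 (18 per group); f = 0.25; alpha = 0.0167; power 0.80; k = 3 groups; m = 3 measurements.

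**Inputs assumed here because the protocol does not state them:** correlation ρ between repeated measurements, and sphericity (ε = 1). These matter only for step 4.

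**1. Reproduce the plan's 54.**
- 45 × (1 + 0.20) = 54; per group, 15 × 1.2 = 18. This matches exactly.
- 45 / (1 − 0.20) = 56.25, rounded up to 57; per group, 15 / 0.8 = 18.75, rounded up to 19. This does not match.

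Multiplication by 1.2 is therefore the likely route to 54. It is an inference from the numbers, not something the protocol states.

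**2. Apply the stated dropout to the stated enrolment.**
- 54 × 0.80 = 43.2 children; per group, 18 × 0.80 = 14.4.
- Expected shortfall against the requirement: 45 − 43.2 = 1.8 children, or 0.6 per group.

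This holds however 54 was reached, and it does not involve the effect size, alpha or correlation.

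**3. Find the attrition that 54 does cover.**
- (54 − 45) / 54 = 9/54 = 16.7%.
- For comparison, 57 × 0.80 = 45.6 (15.2 per group), which meets the requirement.

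**4. Power, conditional on an assumed correlation.** For the within-between interaction, λ = f² × N × m / (1 − ρ), with numerator df (k − 1)(m − 1) = 4 and denominator df (N − k)(m − 1).

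Check of the plan's base figure: with ρ = 0.5 and ε = 1, N = 45 gives λ = 0.0625 × 45 × 3 / 0.5 = 16.875 on 4 and 84 df, and power 0.8145. Going up in equal groups, 45 is the first total to reach 0.80, so ρ = 0.5 reproduces the stated 45. The protocol still does not state that value.

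Power if only completers count, at alpha 0.0167 and f = 0.25:

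| Assumed ρ | 45 completers | 43 completers |
|---|---|---|
| 0.4 | 0.715 | 0.687 |
| 0.5 | 0.8145 | 0.789 |
| 0.55 | 0.864 | 0.842 |

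At ρ = 0.5, the expected 43.2 completers give 0.792, and 44 completers already give 0.802. Against the 0.80 target, the expected loss is 0.80 − 0.792 = 0.008, which is under one percentage point. The difference between rows of the table is much larger than the difference between its columns.

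**The case against.** The strongest reply is that the slip has almost no consequence. Several parts of that reply stand.

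- **The power loss is tiny.** At ρ = 0.5 it is under one point against the 0.80 target. The requirement of 45 itself includes a little rounding up to equal groups.
- **Dropouts are not total losses.** Under intention to treat with multiple imputation, a child who leaves after the second of three assessments still contributes two observed values. Completer-only power is therefore conservative. Imputation does not, however, recreate outcomes that were never observed, and the section itself chose to add an allowance to protect 45.
- **Alpha 0.0167 does not govern most outcomes.** Statistical analysis applies it to the Wechsler scores and uses 0.05 for the other variables, while Outcome measures has the Wechsler administered only twice. For an outcome measured three times and tested at 0.05, the same model with ρ = 0.5 gives about 0.895 at 43 completers.
- **Adding 20% is a common shorthand.** If that was meant, the error is one of labelling: the sentence calls 20% a dropout rate, and at that rate the arithmetic fails.

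None of this makes 45, 20% and 54 agree.

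A reader might also infer more than the documents support. One such inference is that the trial is materially underpowered because of this step. Another is that the plan's own assumptions put power at a definite figure below 80%. Neither follows: the correlation is not stated, and between 0.4 and 0.55 the power at 43 completers runs from about 0.69 to 0.84. A third inference is that 57 families must be enrolled. That is what a true 20% allowance would take, but correcting the statement does not depend on it.

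**Conclusion.** Wrong as written, and minor. The enrolment of 54 covers 16.7% attrition. At the stated 20%, about 43 children are expected to complete (14.4 per group), 1.8 fewer than required; a 20% allowance would have needed 57 in total, 3 more than planned. This conclusion uses only the three printed figures and no outside assumption.

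That 54 came from multiplying by 1.2 is inferred. Any statement about power rests further on an unstated correlation and on sphericity. At the one correlation that reproduces 45, the power with 43 completers is about 0.79, and the partial data kept by the planned analysis make that a conservative value. Neither the design nor the analysis method is called into question by this point.

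**What to change.** Reword the attrition sentence in Sample size in one of two ways:

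- say that enrolling 54 (18 per group) allows for 16.7% attrition from a requirement of 45; or
- keep the 20% and say that about 43 children are then expected to complete, short of the required 45.

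If a power figure is added, state the correlation and sphericity it assumes and give a range. For example, at alpha 0.0167 and f = 0.25, completer-only power at 43 is about 0.69, 0.79 and 0.84 for correlations of 0.4, 0.5 and 0.55. Say also that it is conservative given the planned imputation.

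The cost is one sentence, and the stated allowance becomes slightly less favourable. No change to enrolment, conduct or analysis is needed.
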